QOL will be assessed with the EQ-5D and Short Form (SF) 36 questionnaires before surgery and 1, 3, 6, and 12 months after surgery. Depending on the patient’s preference, the questionnaires are sent to the patient by email or conventional mail, or the patient is called by an interviewer. Patients who do not respond will receive a maximum of two phone calls as a reminder. Before contacting or sending the questionnaires to the patient, confirmation will be obtained that the patient is still alive.

Both healthcare costs (treatment costs including equipment, hospital stay, and re-interventions) and non-healthcare costs (costs as a result of absence from work) will be analyzed. Additional equipment and staff costs associated with EGDT will be monitored to assess incremental costs associated with EGDT. Direct healthcare costs will be calculated by multiplying the volume of (healthcare) resources use with its cost, using standard reference prices for economic evaluation in healthcare whenever available. Information on the following direct costs will be collected from the medical records: blood sample measurements, cultures and other investigations (such as chest films, CT-scans, echography, and ECG), interventions (such as reoperation, catheterization, chest drainage, and antibiotic treatment), and discharge destination (home, nursing home, rehabilitation). Data on absenteeism from work will be collected using parts of the Short-Form Health and Labor Questionnaire (SF-HLQ). The following three questions are added to the SF-HLQ: how many times did you visit your general practitioner? How many times did you visit a doctor in the hospital? Have you been admitted to the hospital? These questions are included in the QOL questionnaire described above. Indirect costs associated with production losses will be estimated using the friction cost method.

Long-term outcome is determined with a letter to the general practitioner of the patient after 3, 6, and 12 months. In this way, mortality and morbidity in the period between 30 days and one year after the operation is determined.

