### Statistical analysis and sample size calculation

A study of the hospital data of one of the participating centers revealed that the number of major complications embedded in the composite primary endpoint was 0.58 per patient, and that a Poisson distribution was applicable. We aim to reduce the number of major complications per patient by 30% (from 0.58 to 0.41). Using Poisson regression with an assumed two-sided error of 5%, we calculated that a sample size of 226 patients in each group will be needed to detect this reduction with a power of 80%. For the multicenter character of the study, a 20% correction was made, since the variance between the participating centers is unknown. This results in a total sample size of 542, or 271 patients in each group.

Statistical analysis will be performed using SPSS version 21.0 for Windows (SPSS Inc, Chicago, Illinois, United States). The first analysis will be performed by combining the results from the participating centers. After this, the results of the individual centers are analyzed to detect possible differences. The primary analysis consists of a comparison of the primary endpoint (number of complications per patient) between the control group and the EGDT group using Poisson regression. According to secondary endpoints, data will be checked for normal distribution and presented as mean +/-standard deviation when normally distributed, and as median +/-interquartile range when not normally distributed. Relative risks are presented with 95% confidence intervals. Categorical data are tested with Fisher’s exact test. Continuous data are tested with the independent samples t-test when normally distributed, and with the Mann-Whitney U test if not normally distributed. A *P* value <0.05 is considered statistically significant. Analysis will be carried out according to the intention-to-treat principle.

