For the quality-of-life assessment, the mean EQ-5D score and the individual SF-36 subscale scores are determined, and a comparison will be made between the standard group and the EGDT group. In addition, mean change scores are determined and evaluated over time. For the economic evaluation, especially the EQ-5D, is of importance as utilities and consequently, quality-adjusted life years (QALY), can be elicited using this generic quality-of-life questionnaire. The incremental cost-effectiveness ratio (ICER) will be expressed as cost differences between groups divided by differences in numbers of serious complications between groups (cost per complication averted). The incremental cost-utility ratio (ICUR) will be expressed as cost differences between groups divided by differences in QALY’s gained between groups (cost per QALY). Confidence intervals will be determined using bootstrapping. A cost-effectiveness acceptability curve will be drawn using this bootstrap sample.

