#### Discharge criteria

The length of stay in the hospital and ICU/PACU are important secondary endpoints, since they reflect the clinical course in the postoperative period and represent a significant part of the healthcare costs per patient. The discharge from patients from the hospital or ICU/PACU is, however, not only based on medical conditions but also influenced by the availability of care at the discharge destination. Continuation of care after treatment in the ICU/PACU depends on the capacity of the wards or intermediate care units. Discharge from the hospital may require adjustments at home or (temporary) placement in nursing homes. In addition, discharge from the IC/PACU occurs mainly the morning after surgery, which leads to a skewed distribution. To account for these effects, fit-for-discharge criteria from the hospital and ICU/PACU were determined (Additional file 3) [5].

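### A normality check on the trial data picks the test and summary for every continuous secondary outcome, so EQ-5D and quality-of-life change scores, which the protocol reports as means, can get a Mann-Whitney P value that does not test those means

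*Protocol article*

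**What the plan says.** All of this stands in the protocol article, section Statistical analysis and sample size calculation, unless another section is named.

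- **Summary rule.** It covers the secondary endpoints and reads: "data will be checked for normal distribution and presented as mean +/-standard deviation when normally distributed, and as median +/-interquartile range when not normally distributed".
- **Test rule.** "Continuous data are tested with the independent samples t-test when normally distributed, and with the Mann-Whitney U test if not normally distributed". Neither rule excepts any outcome. No method or level is given for the check.
- **Quality of life.** The last paragraph of the section sets this out as "the mean EQ-5D score and the individual SF-36 subscale scores are determined, and a comparison will be made between the standard group and the EGDT" (the intervention arm). For change over time, it adds: "mean change scores are determined and evaluated over time". It names no test. Under Data collection, EQ-5D and SF-36 are measured before surgery and at 1, 3, 6 and 12 months.
- **Economic evaluation.** The cost-effectiveness ratio is "expressed as cost differences between groups divided by differences in numbers of serious complications between groups (cost per complication averted"). The cost-utility ratio uses the QALY difference in the same way. Confidence intervals come from a bootstrap, with an acceptability curve.
- **Length of stay.** The section Discharge criteria expects a skewed ICU/PACU stay. It says that lengths of stay "represent a significant part of the healthcare costs per patient". No section asks for mean stay as an outcome estimate.

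**The concern.** The two paragraphs do not fit together for quality of life. EQ-5D is bounded, so at 271 per arm it can be expected to fail a formal normality check. The general rule then calls for a median and a Mann-Whitney test, while the quality-of-life paragraph calls for a mean. Mann-Whitney tests whether a patient in one group tends to score higher than a patient in the other; it does not test a difference in means. The report could show a mean difference beside a P value for a different quantity.

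The second problem is stability. For a scale with slight skew, where the t-test works well at this size, the outcome of the check varies by chance. The same scale could be reported as a mean with a t-test at one visit and as a median with Mann-Whitney at the next. Results over time would then not be comparable, and the switch gains nothing.

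**Working it through.** **1. Patients per arm.** Inputs from the plan: base rate 0.58, a 30% reduction (rate ratio 0.7), two-sided 5%, power 80%, 1:1 allocation. The Poisson-regression formula (Signorini) gives the total as

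N = (1.960·√4 + 0.8416·√(2 + 2/0.7))² / (0.58·(ln 0.7)²) = (3.920 + 1.855)² / 0.0738 ≈ 452, or 226 per arm.

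Then 226 × 1.2 = 271.2 and 452 × 1.2 = 542.4. The plan's 226, 271 and 542 all reproduce. The steps below use n = 271 per arm.

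**2. How stable is the check?** Assumptions: Shapiro-Wilk at 5% and gamma-shaped data. Share of simulated samples of 271 in which normality is rejected:

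| Skewness | One sample tested, p | Either arm tested, 1 − (1 − p)² |
|---|---|---|
| 0.2 | 20% | 1 − 0.80² = 36% |
| 0.4 | 66% | 1 − 0.34² = 88% |
| 0.6 | 95% | 1 − 0.05² ≈ 100% |

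Direct simulation of the either-arm version gave 36% to 38% at skewness 0.2 and 65% to 68% at skewness 0.3.

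If two visits were independent, they would get different tests with probability 2p(1 − p). At p = 0.36 this is 2 × 0.36 × 0.64 = 46%; at p = 0.66 it is 2 × 0.66 × 0.34 = 45%. The same patients answer at each visit, so the real figure is likely to be lower.

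**3. Bounded or strongly skewed outcomes.** In simulated arms of 271, a bounded EQ-5D model (shape assumed) failed Shapiro-Wilk in 100% of cases. The cost models failed in essentially 100%.

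**4. Is the switch needed for validity?** No. The Welch t-test had a type I error of 4.6% to 4.9% in skewed stay and cost models at this size, and 4.2% in a further cost model.

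**5. What if the rule were also applied to costs?** The documents give no cost figures, so every cost input here is assumed: base cost mean 1 (CV 0.25), cost per complication 0.5 to 3 times base (CV 1), and an added cost d for each EGDT patient of 2% to 20% of base. Complications are Poisson with rates 0.58 and 0.41. With c the cost per complication, the true mean difference is d − 0.17c, because 0.58 − 0.41 = 0.17.

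- Over the whole grid, the sample mean difference and the Mann-Whitney direction were opposite in 1% to 82% of trials.
- With d of 2% to 5% of base they were opposite in 4% to 22%.
- In these runs the true mean and true median differences took opposite signs only where d was 10% of base or more.
- Example, c = 2 and d = 0.20: the true mean difference is 0.20 − 0.34 = −0.14 (EGDT cheaper), and the median difference is +0.07. Directions were opposite in 75% of trials. Mann-Whitney was significant for EGDT being dearer in 43%; in 24% of all trials this came with a lower EGDT sample mean.

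**The case against.** The strongest reply is that a specific paragraph governs over a general one. The economic evaluation has its own method, built on differences and a bootstrap, and no section prescribes a median or a Mann-Whitney test for costs. This stands. A reader might infer that costs are sent to ranks and could reverse the cost-effectiveness conclusion. The document does not support that: the ratios rest on cost and QALY differences whatever the normality check shows. The article does foresee added cost ("Additional equipment and staff costs associated with EGDT will be monitored to assess incremental costs associated with EGDT") but gives no amount, so a reversal is possible under assumed inputs and is not shown.

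A reader might also infer that the plan needs mean length of stay. It does not say so. Stay enters through cost, and median with Mann-Whitney is a defensible convention for stay as an outcome.

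The check could be graphical, so the percentages in step 2 depend on an assumed test. That is fair. A graphical check, however, leaves the choice to judgement, which does not make it more stable.

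It is also tempting to say that an unblinded team picks the test after seeing the data. The Trial design section calls clinicians, patients and observers unblinded and does not mention the analyst. The rule is prespecified and depends on shape rather than on the treatment effect, and no inflation of type I error has been shown for it.

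Finally, the test and interval for each single outcome may be left to an analysis plan that is not shown, so their absence is not counted here. The rule itself, though, is stated in the article, and the objection does not reconcile it with the quality-of-life paragraph.

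**Conclusion.** The point holds for continuous secondary outcomes. It is clearest for EQ-5D and the change scores, where the stated estimate is a mean and the only stated rule can lead to a median and a Mann-Whitney P value. That conflict follows from the text, given that a bounded EQ-5D fails the check; it needs no cost assumption. SF-36 subscales share the problem through their mean change scores. For mildly skewed scales (skewness about 0.2 to 0.4) a formal check would choose the test largely by chance; the size of this rests on the assumed Shapiro-Wilk test and gamma shapes. Counts and ordinal grades are not concerned. This is a cheap and worthwhile improvement to secondary analyses, not a threat to the trial's main conclusion.

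**What to change.** In Statistical analysis and sample size calculation:

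- Remove the normality check as the rule for choosing the test, and fix test and summary for each continuous outcome in advance.
- State that EQ-5D, SF-36, costs and QALYs are exempt from any such rule and are compared as mean differences with 95% confidence intervals: Welch or robust standard errors for the scores, and the bootstrap already planned for costs and QALYs.
- For length of stay, fix median and interquartile range with Mann-Whitney in advance, and add a Hodges-Lehmann estimate with its interval. Mean stay enters through the cost analysis.

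The cost is a few sentences, with no extra data and no change in sample size. The small downside is that mean differences are more sensitive to a few extreme values; medians shown as description cover this.

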The following secondary outcome measures are considered: the grade of major complications occurring in the first 30 days after surgery according to the Accordion Severity Grading system [31]; the number of the following minor complications within the first 30 days after surgery: arrhythmia (requiring intervention), deep venous thrombosis (confirmed by ultrasonography), urinary tract infection (confirmed by urinalysis and treated with antibiotics), prolonged ileus (diagnose made and confirmed by surgeon), herniation or other prolonged wound healing (diagnosis made and confirmed by surgeon); the total amount of fluid administered in the first 24 hours after surgery (crystalloids, colloids, and blood products); inotropic support in the first 24 hours after surgery (amount and duration of infusion); hemodynamic (blood pressure, HR, CI, SVV, mean urine output) and laboratory (central venous oxygen saturation and pCO_2_, serum lactate, troponin) variables in the first 24 hours after surgery; length of stay in the hospital and in the ICU/PACU; continuation of care at intermediate care units (level of care in between the ward and ICU/PACU); number and length of ICU/PACU or intermediate care readmissions; QOL; cost-effectiveness; long-term outcome: 3, 6, and 12 months complications and mortality.

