A number of other outcome measures have been considered as a primary endpoint in this trial. First, we performed a sample size calculation for the detection of a difference in mortality. This however revealed that over 5,000 patients would be needed, which was not feasible. Second, we calculated that approximately 250 patients would be needed to detect a difference in length of stay in the hospital. As a result, the study would have insufficient power to detect differences in terms of morbidity, which was our primary aim. Third, a single complication taken as an outcome measure was considered. In this case, however, consequences for the patient may differ considerably as well. As described previously, pneumonia may have a mild clinical course, but may also result in septic shock with multi-organ failure. Finally, we considered complications weighed according to the Accordian complication severity score as a primary outcome measure [31]. This, however, requires an ordinal approach to data-analysis, which is not straightforward. In addition, it remains difficult to compare patients with multiple complications.

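### Secondary per-patient counts (minor complications, readmissions) are left to a median and a rank test, so no rate ratio comparable with the primary endpoint is planned for them

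*Protocol article*

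**What the plan says.** All references are to the protocol article.

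- **Statistical analysis and sample size calculation.** Poisson regression is named for the primary endpoint only. Secondary endpoints get a normality check and a mean/SD or median/IQR summary. The tests are "Categorical data are tested with Fisher"'s exact test, and "Continuous data are tested with the independent samples t-test when normally distributed, and with the Mann-Whitney U test if not normally distributed". Relative risks with 95% confidence intervals are also promised, without saying for which endpoints. The text then gives quality of life and costs rules of their own.
- **Outcome measures, list after Table 2.** The secondary endpoints include "the number of the following minor complications within the first 30 days after surgery", the number of ICU/PACU or intermediate care readmissions, and "the grade of major complications occurring in the first 30 days after surgery according to the Accordion Severity Grading system".
- **Discussion, Primary endpoint.** The authors prefer the number of complications per patient to the share of patients with at least one, because the number carries information on severity. They considered an Accordion-weighted primary endpoint and set it aside: "This, however, requires an ordinal approach to data-analysis, which is not straightforward".

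**The concern.** The number of minor complications per patient is the same kind of variable as the primary: events per patient over 30 days. It is named as a secondary endpoint in the Abstract and the Objective, and the Background says minor complications should be evaluated separately from major ones. The protocol treats the major count as needing a count model, but sends its companion endpoint through a normality check.

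A sparse count will fail that check. It would then be shown as a median with interquartile range and tested by ranks. If events are rare, both arms read 0 and the reader cannot see the direction or size of a difference. Major complications would have a rate ratio and minor complications would have nothing on the same scale. At stake is how interpretable a secondary result is, not whether its test is valid.

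**Working it through.** **1. Inputs from the document.** "We aim to reduce the number of major complications per patient by 30% (from 0.58 to 0.41"), two-sided 5% level, 80% power, 226 per group, raised by 20% to 271 per group (542 in total). No rate is given for minor complications or readmissions, and no distribution for the Accordion grade.

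**2. The plan's own figure.** Take the Poisson-regression sample-size formula with a 1:1 covariate and an exact 30% reduction:

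N = [1.96·√4 + 0.8416·√(2 + 2/0.7)]² / (0.58·(ln 0.7)²) = (3.920 + 1.855)² / 0.0738 ≈ 452

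That is 225.98, so 226 per group, and 452 × 1.2 = 542.4. The stated size is reproduced, and nothing below changes it.

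**3. When is the median 0?** For a Poisson count, P(0) = exp(−λ). The median is 0 while exp(−λ) ≥ 0.5, that is λ ≤ ln 2 ≈ 0.69.

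- At 0.58: P(0) = 0.560, median 0, IQR 0–1.
- At 0.41: P(0) = 0.664, median 0, IQR 0–1.
- At 0.70: P(0) = 0.497, median 1.

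At the primary's own rates, the planned summary would be identical in the two arms. In simulated trials with 271 per arm, a 30% reduction and assumed control means of 0.3 to 0.58, both medians were 0 in about 97–100% of trials.

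**4. What a relative risk would show.** Any event versus none at the primary's rates: (1 − 0.664)/(1 − 0.560) = 0.336/0.440 = 0.76. The rate ratio is 0.41/0.58 = 0.71. The relative risk ignores second and later events, which is the information the authors chose to keep for the primary.

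**5. Power, 271 per arm, two-sided 5%.** Analytic check at 0.58 vs 0.41: the log rate ratio is −0.347 and its SE is √[(1/0.58 + 1/0.41)/271] = 0.124. Power is Φ(0.347/0.124 − 1.96) ≈ 80%. Simulation (rates other than 0.58/0.41, and all overdispersion, are assumptions):

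| Control / treated mean | Distribution | Count regression | Mann-Whitney | Any vs none |
|---|---|---|---|---|
| 0.58 / 0.41 | Poisson | 80.7% | 77.3% | 70.2% |
| 0.40 / 0.28 | Poisson | 66.2% | 63.0% | 59.5% |
| 0.30 / 0.21 | Poisson | 54.4% | 51.6% | 49.6% |
| 0.30 / 0.21 | gamma-mixed, shape 1.5 | 48% (robust) | 44% | – |
| 0.40 / 0.28 | gamma-mixed, shape 1.5 | 59% (robust) | 54% | – |
| 0.60 / 0.42 | gamma-mixed, shape 1.5 | 71% (robust) | 62% | – |
| 0.58 / 0.41 | gamma-mixed, variance 1 | 64.0% (robust) | 55.4% | 47.8% |

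The shape-1.5 rows use 2,000 simulated trials each and the other rows 20,000.

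**6. Type I error.** With no effect, a mean of 0.58 and gamma variance 1, the model-based Poisson test rejects in 11.8% of trials, the robust version in 5.1% and Mann-Whitney in 5.0%. Moving to a count model is therefore an improvement only with robust standard errors.

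**7. Accordion grade.** Assume a seven-level per-patient scale with 56% free of complications. An unordered test (chi-square standing in for Fisher) has 48.7% power against 79.1% for a rank test at odds ratio 1.6, and 37.8% against 66.4% at 1.5. An assumed five-level scale at 1.6 gives 56.8% against 78.0%. These gaps matter only if the grade were tested without its order, which the document does not say.

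**The case against.** Three stronger readings are tempting, and the document does not support them.

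- *The Accordion grade goes to Fisher's test.* A reader might infer this because a grade looks categorical. The text assigns it to no test. Mann-Whitney, which uses order, is already in the plan, and the Discussion shows that the authors know these data are ordinal. Under that reading the loss in step 7 disappears.
- *Secondary counts have no effect measure at all.* Relative risks with 95% CI are promised. The endpoints are not named, and for a count the measure would at best be any versus none, but the plan is not silent.
- *The rank test costs material power.* The loss is small for Poisson counts and moderate only under assumed overdispersion. Mann-Whitney holds its level, which a model-based Poisson test may not. A rank test for an unpowered secondary count is defensible.

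It can also be said that endpoint-level methods belong in the analysis plan, which is not shown, and that a condensed article need not list them. That limits the weight of the point. It does not remove it, because the article states a positive rule for secondary endpoints and reserves the count model for the primary. The 0-versus-0 summary is conditional on rates that the document does not give.

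**Conclusion.** The point holds in a limited form. The stated rule does not suit the secondary per-patient counts: if their means are below about 0.69 (Poisson), both arms would be summarised as median 0, and no rate ratio comparable with the primary's is planned. The cost in power is about 3 to 4 points for Poisson counts and about 4 to 9 under assumed overdispersion, for a reduction of about 30% with 271 per arm. The case for change rests mainly on interpretability. The absence of a named method for the Accordion grade is a minor gap to close, not a wrong test. The primary analysis, the sample size and the validity of the planned tests are unaffected.

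**What to change.** In Statistical analysis and sample size calculation, add wording such as:

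*Secondary per-patient counts (minor complications, readmissions) are analysed with the same log-link count regression as the primary endpoint, with robust standard errors, and reported as mean counts per arm and a rate ratio with 95% confidence interval.*

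As a clarification, add: *The Accordion grade is compared with a method that uses its order (the Mann-Whitney test or a proportional-odds model).* It would also help to name the endpoints for which relative risks are reported.

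The cost is two or three sentences. No new data or patients are needed, and the software named in the plan fits these models. If the analysis plan already says this, the article's general rule only needs to point to it.

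### EQ-5D and SF-36 are to be measured before surgery, but the stated comparison uses raw means and change scores, giving up precision that baseline adjustment would provide

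*Protocol article*

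**What the plan says.** Under Data collection, the protocol article schedules both instruments at baseline and four later times: "QOL will be assessed with the EQ-5D and Short Form (SF) 36 questionnaires before surgery and 1, 3, 6, and 12 months after surgery".

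Under Statistical analysis and sample size calculation, the quality-of-life paragraph says that "the mean EQ-5D score and the individual SF-36 subscale scores are determined, and a comparison will be made" between the standard and EGDT groups, and then: "In addition, mean change scores are determined and evaluated over time". The same section names the tests for continuous secondary data: "Continuous data are tested with the independent samples t-test when normally distributed", and "with the Mann-Whitney U test if not normally distributed". No covariate is mentioned for any of these comparisons.

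For the economic evaluation, the section says that QALYs are derived from the EQ-5D, defines the cost-utility ratio as the cost difference over the QALY difference, and plans bootstrap intervals. It does not describe how QALYs are calculated or how their difference is estimated.

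**The concern.** A preoperative score is usually one of the strongest predictors of the same score after surgery. A comparison of raw means does not use it. A change score subtracts it in full, which over-corrects whenever the correlation with follow-up is below 1. A model with the baseline as covariate estimates how much to subtract.

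The article also gives two summaries, raw and change, without saying which one carries the conclusion. When the arms differ at baseline by chance, the two can give different answers.

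The precision matters because the sections Previous literature and Added value of the proposed study present quality of life and cost-effectiveness as what this trial adds to earlier ones. The section RCT design says that center and type of surgery may influence outcome strongly. They are used to stratify randomization, but the two-group tests leave them out.

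**Working it through.** **The plan's own figures.** The article gives no precision or power for quality of life. Its only sample size is for the primary endpoint, and it supplies the n used below. The Poisson-regression formula with a 0.58 rate, rate ratio 0.70, two-sided 5% and 80% power gives

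N = [1.96·√4 + 0.8416·√(2 + 2/0.70)]² / [0.58·(ln 0.70)²] ≈ 452, or 225.98 per group.

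This matches the stated 226. Then 452 × 1.2 = 542.4, which gives 542 in total and 271 per group.

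**Inputs.** n = 271 per group (document). Assumptions not in the documents: r = 0.3, 0.5 and 0.7, equal standard deviation at baseline and follow-up, and complete data.

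**Formulas.** In units of the score's variance, the group difference has variance (2/n) × V, where

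- raw means: V = 1
- change scores: V = 2(1−r)
- baseline-adjusted: V = 1−r²

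Adjustment is never worse than either. 1−r² cannot exceed 1, and 2(1−r) − (1−r²) = (1−r)², which cannot be negative.

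**Results.** SE = √(2V/271), in SD units.

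| r | V raw | V change | V adjusted | SE raw | SE change | SE adjusted | Better planned option | Saving against it |
|---|---|---|---|---|---|---|---|---|
| 0.3 | 1 | 1.40 | 0.91 | 0.0859 | 0.1016 | 0.0820 | raw | 1 − 0.91 = 9% |
| 0.5 | 1 | 1.00 | 0.75 | 0.0859 | 0.0859 | 0.0744 | tie | 1 − 0.75 = 25% |
| 0.7 | 1 | 0.60 | 0.51 | 0.0859 | 0.0665 | 0.0614 | change | 1 − 0.51/0.60 = 15% |

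The saving against the better option is r² up to r = 0.5 and (1−r)/2 above it, so 25% is its maximum. Expressed as patients, the gains are 1/0.91 = 1.10, 1/0.75 = 1.33 and 0.60/0.51 = 1.18 times the number analyzed. The formulas concern differences in means; they do not describe the Mann-Whitney test exactly.

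**QALY, conditionally.** Suppose the QALY were the trapezoid area over 0, 1, 3, 6 and 12 months, with equal correlation r between all times and no baseline adjustment. The baseline score has weight 1/24 = 0.042, so the share of a baseline utility imbalance expected to carry into the QALY difference is 0.042 + 0.958r: 0.33, 0.52 and 0.71 at the three values of r. Chance imbalance with 271 per group has a 95% range of 1.96 × √(2/271) = ±0.168 SD. For an assumed utility SD of 0.15 to 0.30, the carried amount is ±0.008 to ±0.036 QALY. Adjustment would lower the QALY variance by 22%, 43% and 65%. In simulation the unadjusted difference averaged zero under no effect. These figures show what adjustment would be worth if it is not already intended.

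**The case against.** The strongest reply is that nothing here is invalid. Allocation is randomized, raw and change comparisons both estimate the effect without bias, and the width of the interval already reflects chance imbalance. These are secondary endpoints. All of that stands, and the point is one of efficiency only.

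A second reply is that the phrase about evaluating change over time names no model and could cover a repeated-measures analysis. That is fair as far as it goes. But quality of life is a listed secondary outcome, and the only tests the section names for continuous secondary data are unadjusted. A repeated-measures model of change scores without the baseline as covariate would keep the over-correction.

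Three stronger readings are tempting, and the documents do not support them:

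- A reader might infer that the QALY difference is left unadjusted. The article gives only the definition of the ratio and the use of bootstrapping, which is compatible with an adjusted estimate. An article commonly leaves QALY construction to a fuller plan.
- A reader might infer that deaths drop out and that survivors' means favor the arm with more deaths. Confirming that a patient is alive before each questionnaire says nothing about how deaths are valued. Mortality is followed to 12 months, so the information to include them is planned.
- A reader might quote larger gains, such as 35% at r = 0.3 (against change scores) or 49% at r = 0.7 (against raw means). Each takes the weaker planned summary as comparator.

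**Conclusion.** The point holds as a modest, avoidable loss of precision in the EQ-5D and SF-36 comparisons. Against the better planned summary, adjustment lowers the variance by 9%, 25% and 15% at r = 0.3, 0.5 and 0.7. The direction holds for any r strictly between 0 and 1; the size rests on the assumed correlation, equal variances and complete data. Any further gain from adjusting for center and type of surgery is not quantified. There is no bias in expectation. The handling of QALYs and deaths is not shown to be wrong. The primary Poisson analysis and N = 542 are untouched.

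**What to change.** In the quality-of-life paragraph of Statistical analysis and sample size calculation, replace the raw-mean and change-score comparisons with one stated model: analysis of covariance at each time, or a mixed model for repeated measures over 1, 3, 6 and 12 months. The covariates are the preoperative score, center and type of surgery. Means and mean changes can remain as description. Because baseline questionnaires may not all be returned, add a sentence on how a missing preoperative score is handled.

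As a consistent extension, estimate the QALY difference with baseline EQ-5D utility as a covariate, refitted within each bootstrap sample. State in the same place, or in the fuller economic plan, how QALYs are calculated and how deaths enter.

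The cost is analysis wording. The preoperative questionnaires and stratification factors are already part of the design, so no new visits, data or patients are needed. About 160 patients had been recruited at the end of 2013, with recruitment expected to run to 2016, so the change could be made before the final analysis.
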